
### Methods in analysis to handle protocol non-adherence and any statistical methods to handle missing data {20c}

In the primary clinical analysis, the impact of missing EQ-5D-5L outcome data will be minimised to some extent by using the mixed-effects, repeated measures model, as it allows the inclusion of intermittent responders under the assumption that data are missing at random. Nevertheless, the extent and pattern of missing data for each outcome will be explored and predictors of missingness examined, especially if these vary by intervention. If necessary, multiple imputations will be utilised to impute missing data and explore deviations from the missing at random assumption.

Complier average causal effect (CACE) analyses for the primary outcome will be undertaken to explore the impact of non-compliance on treatment effect estimates. Three analyses are proposed. The first CACE analysis will be conducted on the data of participants who are fully compliant, defined as attendance at three or more of the first six sessions and at least three other sessions. The second CACE analysis will define compliance as attendance at one yoga session or more (i.e. any compliance), which will include participants who are fully and partially compliant. The final CACE analysis will include the number of sessions attended in its continuous form.

### Plans to give access to the full protocol, participant level-data and statistical code {31c}

The full protocol is available via the funder website: https://fundingawards.nihr.ac.uk/award/17/94/36. Requests for other data or documentation should be made by contacting the corresponding author.

### Oversight and monitoring

#### Composition of the coordinating centre and trial steering committee {5d}

The trial coordination team meets regularly with the chief investigator, yoga consultants, and process evaluation team. A Trial Management Group and Trial Steering Committee will oversee the project. The Trial Management Group will typically meet every 2 months and comprises the chief investigator, the co-applicant co-investigators, the trial and data coordinators, a process evaluation researcher, a clinician, a patient representative, and a BWY representative. The Trial Steering Committee will meet approximately every 6–9 months and includes an independent chairperson and members as well as representatives of the Trial Management Group (chief investigator, statisticians, trial coordinators).

#### Composition of the data monitoring committee, its role and reporting structure {21a}

The Trial Steering Committee has agreed to additionally take on the role of the data monitoring committee. A separate data monitoring committee was considered unnecessary due to the low-risk and open nature of the trial. The Trial Steering Committee will review and discuss data pertaining to participant safety and trial progress.

#### Adverse event reporting and harms {22}

Adverse events related to yoga practice or study participation during the 12 months after randomisation will be recorded by trial coordinators following assessment of seriousness, causality, and expectedness by the chief investigator and a clinician co-investigator. We will also record all deaths and all falls that result in hospitalisation, regardless of causality. Yoga teachers and participants are responsible for notifying the trial office of any adverse events. The chief investigator or delegate will report any related and unexpected serious adverse events to the Research Ethics Committee within 15 days of the chief investigator becoming aware of it. Adverse events will be summarised and reported to the Research Ethics Committee, the funder, and the Trial Steering Committee in their regular progress reports.

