### Objectives {7}

The primary objective is to establish if the offer of a 12-week GYY programme in addition to continued access to usual care is more effective compared with usual care alone in improving health-related quality of life (EQ-5D-5L utility index score) over 12 months in adults aged 65 years or over with multimorbidity.

Secondary objectives include the following:
To explore the effect of the GYY programme on health-related quality of life, depression, anxiety, and loneliness at 3, 6, and 12 months after randomisationTo explore the effect of the GYY programme on the incidence of falls over 12 months after randomisationTo explore the safety of the GYY programme relative to control in terms of the occurrence of adverse events over 12 months after randomisationTo assess if the GYY programme is cost-effective, measured using differences in cost of health resource use between the intervention and control groups and the incremental cost-effectiveness ratios using quality-adjusted life years (QALYs) derived from the EQ-5D-5L measured at 3, 6, and 12 months after randomisationTo undertake a qualitative process evaluation to describe the experience of the intervention, explain the determinants of delivery (including treatment fidelity), and identify the optimal implementation strategies for embedding and normalising the GYY programme in preparation for a wider roll-out

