The delivery mode of the 12-week intervention will be either face-to-face or online. Online classes address the need for social distancing during the COVID-19 pandemic. The trial classes will comprise intervention participants only, with each 12-week course having 12 participants allocated if delivered online and up to 15 participants if delivered face-to-face. Face-to-face classes will be conducted in non-medical community-based facilities (e.g. yoga studio, community hall, leisure centre) following checks of venue suitability by the trial team. Accessibility factors to consider include close proximity to public transport links, parking facilities, and disability access. Online classes will be conducted via Zoom, an online livestream platform freely accessible to participants using a computer or tablet. Participants will be advised to activate their cameras so that the teacher is able to view them and provide feedback on their technique. Prior to online classes commencing, the yoga teacher will conduct one-to-one Zoom meetings with their students to optimise the set-up of their equipment and environment and to discuss any health issues or course queries. Participants will also be able to ask questions throughout the course.

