#### Secondary outcome measures

The following are the secondary outcome measures:
HRQoL at 3, 6, and 12 months after randomisation using the EQ-5D-5L utility score.HRQoL at 3, 6, and 12 months and overall using the PROMIS-29 [29].Depression severity at 3, 6, and 12 months and overall using the Patient Health Questionnaire-8 [30].Anxiety severity at 3, 6, and 12 months and overall using the Generalised Anxiety Disorder-7 [31].Loneliness at 3, 6, and 12 months and overall. Four questions are used to capture different aspects of loneliness. The first three questions are from the University of California, Los Angeles (UCLA) 3-item loneliness scale [32]. The wording of the UCLA questions and response options are taken from the English Longitudinal Study of Ageing. The last is a direct question about how often the respondent feels lonely.The incidence of falls over 12 months assessed via self-report at 3, 6, and 12 months.Adverse events over 12 months.Resource use data will be collected to inform the economic evaluation from patient questionnaires and GP practice records (i.e. medication data).

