### Statistical methods

#### Statistical methods for primary and secondary outcomes {20a}

Statistical analyses will be described in detail in a statistical analysis plan (SAP) that will be agreed upon with the Trial Steering Committee before all data has been collected. Any subsequent amendments will be clearly stated and justified. The trial will be reported in accordance with the Consolidated Standards of Reporting Trials (CONSORT) guidelines for clinical trials [36]. Baseline data will be summarised using descriptive statistics with no formal statistical comparisons of the baseline data undertaken. All analyses will be conducted on an intention-to-treat basis and using two-sided significance tests at the 5% significance level, unless otherwise stated.

The primary outcome will be analysed using a linear mixed model, including all available follow-up time points. The model will adjust for EQ-5D-5L at baseline and include as fixed effects: time point, trial arm, arm by time interaction, and other covariates specified in the SAP. Patient (to account for the repeated measures) and site will be included as random effects. The overall difference between the two groups over the 12 months from randomisation will be the primary endpoint, but differences at each time point will be extracted for secondary investigations aimed at determining the potential pattern of change. Adjusted mean differences will be presented with an associated 95% CI and *p* value. Different covariance patterns for the repeated measurements will be explored, and the most appropriate pattern will be used for the final model. Model assumptions will be checked, and if they are in doubt, transformations of the outcome data will be considered. Analyses to account for possible clustering by yoga class will also be undertaken by including the class as a random effect, nested within the treatment arm. We shall explore the impact of differing modes of delivery (face-to-face, or online) within subgroup analyses.

The anxiety, depression, loneliness, and PROMIS-29 data will be analysed in the same way as described for the primary outcome. The number of falls experienced by participants over the 12 months will be analysed using a negative binomial regression model. The number and type of serious and non-serious adverse events will be summarised descriptively by randomised group.

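### Apart from deaths and hospitalised falls, adverse events are recorded only if judged related to yoga or study participation, so the by-group safety summary is not like for like

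*Protocol article*

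**What the plan says.** Four places in the protocol article bear on this.

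- **Objectives {7}** include exploring the "safety of the GYY programme relative to control in terms of the occurrence of adverse events over 12 months".
- **Secondary outcome measures** list "Adverse events over 12 months", with no restriction to related events.
- **Statistical methods {20a}** state: "The number and type of serious and non-serious adverse events will be summarised descriptively by randomised group".
- **Adverse event reporting and harms {22}** sets the recording rule: "Adverse events related to yoga practice or study participation during the 12 months after randomisation will be recorded by trial coordinators". Recording comes only once each event has been judged for how serious it is, what caused it and whether it was expected. The section then makes two exceptions: "We will also record all deaths and all falls that result in hospitalisation, regardless of causality". On notification it says: "Yoga teachers and participants are responsible for notifying the trial office of any adverse events".

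The intervention description {11a} adds: "The trial classes will comprise intervention participants only".

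**The concern.** The objective, the outcome and the summary are written as a comparison of adverse events between arms. The recording rule lets most events through only if they are linked to yoga or to being in the study. In the intervention arm there is a 12-week yoga course, plus home practice, to which an event can be linked. In the control arm there is little beyond questionnaires and any yoga that participants take up themselves. The same event in the same kind of person can therefore enter the table in one arm and not in the other.

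Two things are at stake. A reader who compares the columns may take an excess with yoga as evidence of harm when it comes from the recording rule. And the table cannot show a benefit in events that the rule drops, such as admissions for reasons other than a fall. The Trial Steering Committee, which also acts as data monitoring committee, receives adverse event summaries under the same rule.

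**Working it through.** **Plan's own figure.** The article states no adverse event rate or count, so there is none to reproduce. The only figure used below is the number per arm. The sample size section {14} gives a difference of 0.06, SD 0.20, 90% power, two-sided 5% and 20% loss: n per arm = 2 × (1.960 + 1.282)² × 0.20² / 0.06² = 233.5, rounded up to 234. Then 234 / 0.8 = 292.5, rounded up to 293 per arm, or 586 in total, as stated. The concern does not depend on this calculation.

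**Step 1: how an event enters the summary in each arm.**

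| | Intervention arm | Control arm |
|---|---|---|
| Notifiers {22} | Participant and yoga teacher | Participant |
| Regular contact with a notifier other than the participant | Usually a weekly class for 12 weeks {11a} | None described |
| Yoga exposure that can make an event related | Trial classes, home practice, any own yoga | Any own yoga only |
| Study participation that can make an event related | Yes | Yes |
| Deaths, hospitalised falls | Recorded whatever the cause | Recorded whatever the cause |

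The one-off class offered to some controls {18b} takes place after the final follow-up, so it adds no exposure within the 12 months.

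**Step 2: what the rule removes.** The two exceptions are both serious outcomes. Every non-serious event in the planned summary has therefore passed the relatedness filter. So has every serious event other than a death or a hospitalised fall. In adults aged 65 or over with at least two chronic conditions, admissions for other reasons are to be expected, and they drop out unless judged related.

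**Step 3: direction.** Let r be the all-cause proportion with an event, equal in both arms, and let f be the share of those events judged related. Then

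recorded events = 293 × r × f.

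With r equal, the ratio of recorded counts is f in the yoga arm over f in the control arm. It reflects the filter, not total harm.

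**Step 4: illustration only.** All values of r and f here are assumptions.

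| r (both arms) | f yoga | f control | Recorded, yoga | Recorded, control |
|---|---|---|---|---|
| 10% | 5% | 0% | 1.5 | 0.0 |
| 10% | 20% | 1% | 5.9 | 0.3 |
| 30% | 10% | 1% | 8.8 | 0.9 |
| 50% | 5% | 0% | 7.3 | 0.0 |
| 50% | 20% | 1% | 29.3 | 1.5 |

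Across this range the yoga column reads about 1.5 to 29 and the control column 0 to 1.5, with no true difference in all-cause events. The width of the range shows that the document cannot fix the size of the distortion. Its direction follows whenever f is larger in the yoga arm.

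**Step 5: what is collected in both arms regardless of cause.** Falls are self-reported at 3, 6 and 12 months and analysed by negative binomial regression. Inpatient episodes and A&E admissions are cost components in the cost-effectiveness analysis, with participant questionnaires as the source and a health service diary given to all participants {18a}. Deaths and hospitalised falls come from the adverse event recording. The material for a like-for-like comparison largely exists, but the safety objective is not tied to it.

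**The case against.** A reader might infer that only related events are recorded and that safety relative to control cannot be assessed at all. The documents do not support that. Deaths and hospitalised falls are kept in both arms whatever the cause, all self-reported falls have a formal between-arm model, and hospital use is collected in both arms.

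A reader might also infer that control counts must be zero. That is not so either. The rule refers to yoga practice in general, not to trial classes. No concomitant activity is prohibited {11d}, yoga outside the trial is asked about at follow-up, and one sub-study addresses contamination. Study-related events can also occur in either arm.

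Nor would it be fair to attach a p-value to assumed counts. The objective is to explore, the summary is descriptive and no test of adverse events is planned.

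Further points have weight. Participants in both arms are asked to notify any event, so the filter acts at recording and not at notification. The full protocol, which is not shown, may say more on how events are solicited and logged. Limiting collection to related events can also be reasonable in a trial that the article describes as low-risk.

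These arguments limit the point but do not remove it. The article's own recording rule conflicts with its unqualified comparative objective, outcome and by-group summary. Falls incidence is a separate objective in {7} and does not supply the adverse event comparison. An unfiltered notification does not help if unrelated events are then not recorded.

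**Conclusion.** The point holds in limited form. Apart from deaths and hospitalised falls, the planned by-group adverse event summary counts events through a filter that depends on exposure to yoga, with an additional notifier in one arm. It is not like for like, it will tend to show an excess with yoga even if all-cause harm is equal, and it does not match the objective or the outcome as listed.

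This rests on the recording rule as printed and on control participants practising less yoga than the intervention arm. The size of the bias cannot be computed from the document, and the counts above are illustrations. The primary endpoint, the sample size and all planned tests are unaffected. This should be fixed, but it does not threaten the trial's main conclusion.

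**What to change.** 1. Base the between-arm safety comparison on events captured regardless of cause under the same rule in both arms. These are deaths and hospitalised falls from the adverse event recording, self-reported falls, and all-cause inpatient episodes and A&E admissions from the resource-use data. The questionnaires cannot supply deaths, and the article does not say that they identify falls leading to hospitalisation. Those two must continue to come from the adverse event recording.
2. Report events judged related to yoga or study participation in a separate table, labelled as non-comparative.
3. Reword the safety objective in {7} and the by-group summary in {20a} to match, and state in the outcome list which adverse events are meant.

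The cost is changes of wording and one extra descriptive table from data already being collected. The limitations are that admissions are self-reported in an open trial, and that teachers may still notify some hospitalised falls in the intervention arm that would go unnotified in the control arm. Both should be stated beside the table.

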#### Frequency and plans for auditing trial conduct {23}

The trial office and sponsor monitor the aspects of the study on an ongoing basis. The Trial Steering Committee will meet approximately every 6–9 months.

#### Plans for communicating important protocol amendments to relevant parties (e.g. trial participants, ethical committees) {25}

Important protocol modifications are those that are likely to significantly affect the safety of the participants, the scientific value of the study, or the conduct or management of the study. These substantial amendments will be submitted to the Research Ethics Committee for approval having been agreed with the funder, sponsor, Trial Steering Committee, and Trial Management Group. Minor modifications to the protocol will be agreed upon with the Trial Management Group and sponsor before submission for approval to the Research Ethics Committee. All amendments will be implemented following the guidance of the Health Research Authority. Trial participants will be written to, where necessary, to explain any changes. All amendments whether substantial or not will be listed in the published final report to the funder.

#### Dissemination plans {31a}

We will develop a publication and dissemination plan to include conference presentation(s) and journal publication(s). We will send a written summary of the trial results to all participants who request this on their final follow-up questionnaire. We will also plan dissemination to the relevant patient and clinical interest groups.

This protocol is being made publicly available. It is planned for a full trial report to be submitted to the funder and for publication in a peer-reviewed journal. The full trial report will be open access and made available as a permanent archive in the NIHR Journals Library. At the time of publishing the protocol, there was no plan to make the anonymised participant-level dataset and statistical code for generating the results publicly available. However, external requests for this data and code will be considered by the Trial Management Group after the publication of the main trial findings.

The criteria for authorship and contributorship will be taken from the International Committee of Medical Journal Editors [49]. Those who did not design the study or contribute to drafting the work but were involved in the trial conduct (e.g. yoga teachers and staff at recruiting practices) will be acknowledged as collaborators. When a journal permits, we will list all authors rather than use a group name. There will be a designated writing group for each publication and one or more lead writers who convene the group. Any member of the trial team can propose a publication to the chief investigator, lead trial coordinator, and senior member of the York Trials Unit. For each publication, all members of the trial team will be asked whether they consider themselves to be a potential author, contributor, or neither. The chief investigator, lead trial coordinator, and senior member of the York Trials Unit will then agree on the attributions. There are no plans to use professional medical writers to assist with the preparation of trial reports or publications.

## Discussion

Multimorbidity is common in older adults and associated with high levels of illness burden and healthcare expenditure [4–7]. We know from previous work and from reviews that there is a lack of evidence-based interventions for older adults with multimorbidity [8, 9]. Yoga might be a useful intervention because it is low-cost, simple, and can address several medical conditions simultaneously. However, many of the previous research studies on yoga have limitations, including small sample sizes, a single yoga teacher delivering the programme, and short-term follow-up. In addition, few studies have focused on older adults with multimorbidity. We have successfully completed a pilot trial that demonstrated the feasibility and acceptability of the GYY programme in this population [21]. The current full-scale trial will build on this previous work by evaluating the clinical and cost-effectiveness of this intervention.

Should the trial demonstrate the GYY programme to be clinically and cost-effective, we will have the necessary information from our process evaluation to identify optimal implementation strategies for embedding and normalising the intervention beyond the study. Easy integration into routine care pathways should be possible, potentially using models and referral processes adapted from those used in exercise referral and social prescribing schemes.

### Trial status

Recruitment to the trial opened on 16 August 2019 and is due to end in September 2021 with follow-up completed by the end of September 2022. The current protocol is version 1.5 (dated 09/07/2020).

## Abbreviations

BWY: British Wheel of Yoga
BWYQ: British Wheel of Yoga Qualifications
CACE: Complier average causal effect
CI: Confidence interval
CONSORT: Consolidated Standards of Reporting Trials
EQ-5D: EuroQol 5 Dimensions
GDPR: General Data Protection Regulation
GP: General practitioner
GYY: Gentle Years Yoga
HRQoL: Health-related quality of life
ICER: Incremental cost-effectiveness ratio
ISRCTN: International Standard Randomised Controlled Trial Number
MD: Mean difference
NICE: National Institute for Health and Care Excellence
NHS: National Health Service
NIHR: National Institute for Health Research
PROMIS-29: 29-item Patient-Reported Outcomes Measurement Information System®
QALY: Quality-adjusted life year
SAP: Statistical analysis plan
SMD: Standardised mean difference
UCLA: University of California, Los Angeles
